## 4.6. HANDLING OUTLIERS

For the analysis of the primary outcome, we do not expect significant outliers based on our definition of population for analysis. Data outliers will be defined as being at least three standard deviations from the mean of its distribution in the variable at that time-point. We will investigate and report the reasons for outliers. Outliers will be included in the analysis and a sensitivity analysis will be conducted by setting outliers to be missing.

## 4.7. MULTIPLE COMPARISONS AND MULTIPLICITY

As the comparisons have been pre-specified, we will not correct for multiple testing. The level of statistical significance will be set at  $p < 0.05$ .

## 5. SECONDARY ANALYSIS

Analysis of the primary analysis population will be repeated with additional adjustments for age, sex and presence of comorbidities (T2DM, hypertension, CVD).

## 6. SUBGROUP ANALYSES

Pre-specified subgroup analyses of the primary outcome will be explored by baseline depression severity (PHQ-9 score: 15-19 [moderately severe] vs. 20-27 [severe]) and duration of depression at baseline split at the median. We will elaborate the primary outcome model by adding a three-way interaction term between trial arm, time, and the subgroup term. We will include all possible two-way interaction terms in this model. As these models are exploratory, we will in any case present treatment effects for each subgroup.

## 7. MECHANISTIC ANALYSES

If results from primary analyses warrant further investigation, a further analysis plan for analyses of mediation and mechanistic variables will be prepared with a view to a further publication.

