| 
Initial descriptive analysis will present the profile of the subjects by study arm without using statistical comparisons. For the primary hypothesis, the change in PHQ-9 scores from baseline to week 6 will be compared between groups. A mixed effect model that includes treatment group, time and their interaction as fixed effects, and individual subjects as random effects will be fit using PHQ-9 at all available assessments. A linear contrast will be used to test the difference between groups in changes from baseline to week 6 in PHQ-9 scores. Two tailed tests and significance level of 0.05 will be used. Secondary outcomes will be analysed using analogous mixed effects generalised linear models. Pre-specified subgroup analyses of the primary outcome will be explored by baseline depression severity (severe versus moderate) and duration of depression at baseline split at the median. Differences in AEs by study arm will be compared and presented as proportions as described in Section I. Safety and differences will be assessed using Fisher's exact test.
 
We will conduct an exploratory mediation analysis using methods described by Valeri & Vanderweele to examine whether adherence to the diet, changes in microbiome, and cortisol awakening response appear to mediate changes in depression assessed by PHQ-9. Extracted faecal information will be sequenced to obtain a global representation of the microbiome compositions, and Alpha diversity will be measured using Observed Species, Whole Tree Phylogeny, and Shannon and Simpson indices. Spearman correlations will determine associations between alpha diversity metrics, individual microbes, and PHQ-9 scores. Kruskal–Wallis one-way analysis of variance tests will be performed to compare relative abundance of the top ten genera, with false discovery rate (FDR) corrections between dietary groups.
 
The extent of missing data will be reported descriptively, including the number of missing data in each group, and baseline characteristics of people with and without missing outcome data. The primary analysis, with mixed models, is valid under the assumption that data is missing at random (MAR). The robustness of the conclusions to the MAR assumption will be tested in sensitivity analyses as below –
 
 
1. Sensitivity analysis assuming everyone with missing outcome data has severe depression
 
2. Sensitivity analysis assuming everyone with missing outcome data has no depression (included for completeness, not for plausibility)
 
 |                                         |                             |

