### 1.2. PURPOSE AND SCOPE OF THE PLAN

The purpose of the plan is to describe the analysis of the primary, secondary, exploratory and mechanistic outcome measures as stated in the protocol. No interim analysis is planned.

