|--------------------|------------------------------------------------------------------|--------------------------------|----------------------|
| Mechanistic | Changes in cortisol level for awakening response                 | Saliva sample (home test kits) | Baseline, week 6     |
| Mechanistic | Changes in gut microbiome for all species                        | Stool samples (home test kits) | Baseline, week 6     |
| Mechanistic | Changes in reward sensitivity                                    | PILT                           | Baseline, week 6, 12 |
| Mechanistic | Changes in the inability to experience pleasure (i.e. anhedonia) | SHAPS                          | Baseline, week 6, 12 |

Note: PHQ-9, Patient Health Questionnaire-9; GAD-7, General Anxiety Disorder Scale; SHAPS, Snaith-Hamilton Pleasure Scale; PDQ-5, Perceived deficits questionnaire-5-item; SF-12, SF Short-Form 12 Health Survey; WSAS, Work and Social Adjustment Scale; PILT, Probabilistic instrumental learning task.

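### SAP Section 7 makes any mechanistic analysis plan depend on an undefined reading of the primary results, which leaves cortisol, microbiome and PILT open to selective analysis and reporting

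*Combined protocol and SAP*

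**What the plan says.** SAP Section 7 is one sentence long. Its operative part reads "If results from primary analyses warrant further investigation, a further analysis plan for analyses of mediation and mechanistic variables will be prepared", with a later publication in view. It names no method, and no criterion for when the results would justify going on.

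SAP 1.2 sets a different scope: "The purpose of the plan is to describe the analysis of the primary, secondary, exploratory and mechanistic outcome measures as stated in the protocol". SAP Table 1 (Section 1.4) labels four outcomes as mechanistic: "Changes in cortisol level for awakening response" and "Changes in gut microbiome for all species" at baseline and week 6, and "Changes in reward sensitivity" (PILT) and anhedonia (SHAPS) at baseline, week 6 and week 12.

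The protocol attaches no condition. Section E states the aim of studying cortisol and the gut microbiome as possible pathways. Section J, item 4 commits to an exploratory mediation analysis "to examine whether adherence to the diet, changes in microbiome, and cortisol awakening response appear to mediate changes in depression assessed by PHQ-9". It adds four alpha-diversity indices and states that "Spearman correlations will determine associations between alpha diversity metrics, individual microbes, and PHQ-9 scores". It also compares the ten most abundant genera between diets by Kruskal–Wallis tests with a false discovery rate correction.

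SAP Section 11, on changes relevant to the analysis, lists only the added week-12 PILT assessment.

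**The concern.** Comparisons of cortisol, microbiome and reward learning between the arms are randomised comparisons. They are valid whatever PHQ-9 shows, and a clear biological shift beside a null PHQ-9 result would be informative. If the decision to plan them depends on the primary result, then so does whether a reader ever sees them.

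Writing the plan after the result also leaves the choice of summary measures open at a point when the direction of the trial is known. SAP 4.7 declines to correct for multiplicity because the comparisons were specified in advance. Analyses planned after the primary result could not rely on that reason.

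Willingness to give saliva, urine and stool samples was a condition of entry (protocol Section F, item 3). What is at stake is therefore whether data that every participant had to agree to provide are reported in full.

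**Working it through.** **1. The passages side by side.**

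| Item | Protocol | SAP |
|---|---|---|
| Cortisol | Aim unconditional (Section E); mediation only (Section J) | Mechanistic in Table 1; no method; conditional (Section 7) |
| Microbiome | Aim unconditional; diversity indices, correlations, genera tests, mediation | Mechanistic in Table 1; no method; conditional |
| PILT | Collected; no analysis method | Mechanistic in Table 1; no method; conditional |
| SHAPS | Secondary (ability to experience pleasure) | Mechanistic **and** secondary; analysed under 4.2 in any case |

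The condition therefore bites on three outcomes, not four. For cortisol and microbiome the SAP withdraws something the protocol had committed to. For PILT neither document gives a method. Section 11 is silent on the deferral.

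**2. The plan's own figure.** Inputs from SAP 2.2 and 4.1: difference 5 points, SD 6, power 90%, two-sided 5%.

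- Normal approximation: n per arm = 2 × (1.96 + 1.2816)² × (6/5)² = 30.3, rounded up to 31 (62 in total).
- With the t distribution: 31.25, rounded up to 32, so 64 in total, as stated.
- Allowing for 35% loss: 64 / 0.65 = 98.5, consistent with 100.

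The sample size is not in dispute. It supplies the inputs for step 3.

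**3. How often a plan would be written.** *Warrant* is undefined. Assume it means a significant PHQ-9 benefit. Let n be the number analysed per arm and d the true difference in points. The chance is about Φ(d/6 × √(n/2) − 1.96). The totals run from 64 (the SAP's target for the primary outcome) to 88 (all randomised).

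| True difference | 64 analysed | 80 analysed | 88 analysed |
|---|---|---|---|
| 0 | 2.5% | 2.5% | 2.5% |
| 2.5 points | Φ(1.667 − 1.96) = 38.5% | Φ(1.863 − 1.96) = 46.2% | Φ(1.954 − 1.96) = 49.8% |
| 5 points | Φ(3.333 − 1.96) = 91.5% | Φ(3.727 − 1.96) = 96.1% | Φ(3.909 − 1.96) = 97.4% |

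The 2.5-point row is an illustration at half the design difference. It is not a figure from the documents.

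**4. Distortion among the analyses that go ahead.** This was simulated with 20,000 trials per setting and 40 per arm. The marker has no true diet effect and an assumed correlation of 0.2 to 0.6 with PHQ-9 change. Among trials that pass the condition, the marker's nominal 5% false-positive rate becomes 8–22% if the diet has no PHQ-9 effect, about 5–6% at 2.5 points and 4–5% at 5 points. The distortion is largely confined to the null case, which passes only 2.5% of the time. The main harm is non-reporting after a null or modest result.

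**5. Multiplicity.** In protocol Section J the false discovery rate correction is attached to the ten-genera comparison. The separate sentence on individual-microbe correlations with PHQ-9 carries none.

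**The case against.** Section 7 speaks of preparing a further plan for a further paper. It does not say that data will be dropped. *Primary analyses* may mean everything under SAP Section 4, which carries that heading, and not week-6 PHQ-9 alone. Making mediation depend on an effect has a basis in the protocol: Section E speaks of the mechanism of an effect if there is one, and Section J calls mediation exploratory. The SAP also promises to report deviations.

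Much of this stands. A reader might infer that these outcomes will be selectively analysed. The documents support only that they are open to it. A reader might also infer that all four mechanistic outcomes are at risk, but SHAPS is not. The protocol supplied does not label PILT as mechanistic, so the charge of departing from the protocol applies to cortisol and microbiome.

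Three replies remain:

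- On either meaning of *primary analyses*, the trigger is still the results.
- The case for conditioning mediation does not extend to simple comparisons between arms.
- The promise covers deviations from the SAP. An analysis left out under Section 7 would follow the SAP, so the promise would not catch it.

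It is tempting to add that adherence must be dropped as a mediator because the two arms follow different diets. Adherence is rated on one scale with no restriction to one arm, and the cited mediation method allows exposure–mediator interaction. Dropping it is a preference, not the correction of an error.

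**Conclusion.** The point holds in this form: a stated rule makes the mechanistic plan depend on an undefined reading of results already known. It contradicts SAP 1.2 and is an undeclared departure from the protocol for cortisol and microbiome. Cortisol, microbiome and PILT are left open to selective analysis and reporting.

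The size depends on what *warrant* means. If it means a significant PHQ-9 benefit, with SD 6 and 64 to 88 analysed, a plan would be written about 2.5% of the time with no effect, 39–50% at 2.5 points and 92–97% at 5 points. A reader might infer from the middle figure that the mechanistic data would usually go unanalysed. That does not follow: it needs the assumed rule and an assumed effect of half the design difference, and at the design difference the plan would nearly always be written.

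The timing is unclear. SAP Section 10 says the trial statistician has reviewed the output for the primary outcome measures. The documents do not show whether arm codes were open by then.

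**What to change.** - Delete the condition in SAP Section 7.
- Specify comparisons between arms of the cortisol awakening response and the microbiome at week 6, and of PILT at weeks 6 and 12. Adjust each for its own baseline and report it whatever the primary result. Name one summary measure for cortisol and one for PILT, since neither document gives one, and state which microbiome measures are compared.
- Apply the false discovery rate correction already used for the ten genera to the individual-microbe correlations with PHQ-9 as well.
- Keep mediation exploratory, under a dated plan.
- Date all of this before unblinding. If arm codes are already open, say so and fix the plan before mechanistic data are linked to arm.
- Declare the change in SAP Section 11.

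The cost is a little more SAP text, the work of choosing the summary measures, and an obligation to report null mechanistic results. No new data are needed.

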## 8. ADDITIONAL EXPLORATORY ANALYSIS

We have not yet planned any additional exploratory analysis.

## 9. ADVERSE EVENTS

Only a serious adverse event (SAE) occurring to a participant will be collected in this study. Serious adverse events will be presented descriptively

- classified by types,
- the relevance of this SAE to the treatment

We will report serious adverse events (SAEs) only, reporting the total number and the total number of people affected by the arm. We expect these to be very rare and will not use inferential statistics.

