The current study proposes to test whether a 6-week ketogenic diet is an effective treatment for treatment-resistant depression. We will aim to recruit around 100 participants with treatment-resistant depression. On completion of baseline assessments, participants will be randomised 1:1 into the KD group or control group. The KD group involves 6-week pre-prepared ketogenic diet (i.e. the ratio of fat to protein and carbs is 4:1) with weekly KD-focused behavioural and nutritional counselling. The control group will receive weekly nutritional counselling to increase vegetable consumption and reduce saturated fat intake. Participants in the control group will receive food vouchers (£20 every two weeks) to help purchase these items. This aims to be a plausible placebo dietary treatment for depression. Usual treatment for depression will continue, and a leaflet material is provided in both groups (**APPENDIX 9. Dietary materials for the intervention group** and **APPENDIX 10. Dietary materials for the control group**). The primary outcome will be assessed by the difference between groups in the change in self-reported depression severity, using the Patient Health Questionnaire-9 (PHQ-9) (**APPENDIX 8. SELF-REPORTED QUESTIONNAIRES**) at 6 weeks. The secondary outcomes are anxiety score, ability to experience pleasure, work and social adjustment, quality of life, and cognitive performance (**APPENDIX 8. SELF-REPORTED QUESTIONNAIRES**) from baseline to 6 weeks. This trial will also investigate potential mechanistic pathways (i.e. changes in cortisol and gut microbiome) that may explain the effect of a KD on depressive symptoms. We will follow participants to 12 weeks to assess whether they are following the assigned diet and the changes in primary and secondary outcomes.

In this study, a special concern is risk of self-harm and suicide, and further assistance and monitoring are in place. PHQ-9 will be completed every two weeks in the first six weeks and asks participants 'Over the last two weeks, how often have you been bothered by thoughts that you would be better off dead, or of hurting yourself in some way?'

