with response options 'Not at all, several days, more than half the days, nearly every day.' Participants that report that they have had such thoughts more than half the days or nearly every day will have their risk of suicide assessed at the weekly telephone call using the procedure outlined in **Section I. Safety** and Error! Reference source not found.. Anyone judged to have a serious risk of suicide where an emergency response is initiated will be counted as having a serious adverse event.

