| Serious Adverse Event (SAE)                           | 
A serious adverse event (SAE) is any untoward medical occurrence that:
 
 
• results in death
 
• is life-threatening
 
• requires inpatient hospitalisation or prolongation of existing hospitalisation
 
• results in persistent or significant disability/incapacity
 
• consists of a congenital anomaly or birth defect.
 
 
Other adverse events that require medical intervention may also be considered a serious adverse event when, based upon appropriate medical judgement, the event may jeopardise the participant and may require medical or surgical intervention to prevent one of the outcomes listed above. This would include threatened suicide that was prevented by an emergency response. Any planned admissions that were scheduled at the start of the study will not be counted as SAEs.
 
NOTE: The term "life-threatening" in the definition of "serious" refers to an event in which the participant was at risk of death at the time of the event; it does not refer to an event which hypothetically might have caused death if it were more severe.
 
All participants will be prompted to self-report SAEs at the weekly dietitian call. At 12 weeks, we will ask participants about hospitalisation in the last 6 weeks and phone participants who describe an episode to elicit the details.
 |

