### 3.2. DEFINITION OF POPULATION FOR ANALYSIS

Primary analysis: Given the nature of the study, all randomised participants with at least one measurement on the outcome of interest will be included in the primary intention-to-treat analysis in the group they were randomised.

Safety analysis (serious adverse event): This will include participants who commenced the ketogenic diet compared with all those who commenced the Phyto diet.

The per-protocol population is characterised by:

- health coaches selecting 'Completely/Every Day' or 'Mostly/Most of the Days', when assessing participants' adherence to the diet, in at least 5 out of the (up to) 6 follow-

up calls. (Note on missing data: participants responding to fewer than 5 calls will not be considered adherent)

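### SAP section 9 reports serious adverse events only, so suicidality below that threshold is never summarised by arm, although PHQ-9 item 9 is scheduled in both arms at five visits

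*Combined protocol and SAP*

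**What the plan says.** **Scope of safety reporting.** SAP section 9 sets the rule: "We will report serious adverse events (SAEs) only, reporting the total number and the total number of people affected by the arm". SAEs are to be shown descriptively, "classified by types" and by their relation to treatment. On testing it says: "We expect these to be very rare and will not use inferential statistics". Protocol Section J.4 had planned more for adverse events by arm, where "differences will be assessed using Fisher's exact test", although protocol Section I.2 does not collect non-serious events.

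**Safety population.** SAP 3.2 says of the SAE analysis: "This will include participants who commenced the ketogenic diet compared with all those who commenced the Phyto diet". It does not say what counts as commencing. The efficacy analysis, in the same section, uses randomised participants with at least one outcome measurement, in their allocated group.

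**The named risk.** Protocol Section E says: "In this study, a special concern is risk of self-harm and suicide, and further assistance and monitoring are in place". Suicidal thoughts on more than half the days, or nearly every day, lead to an individual risk assessment (Sections E and I.3).

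**Where item 9 is held.** Protocol Table 3 and SAP Table 1 schedule the PHQ-9 in both arms at baseline and weeks 2, 4, 6 and 12. The SAP uses it as a total score, as remission (4 or below), as a subgroup and adjustment variable, and in the missing-data scenarios (SAP 1.4, 4.1, 4.2, 4.5 and 6). It never uses item 9 separately.

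**The concern.** The plan collects repeated information on the risk it singles out, acts on it person by person, and then does not report it by arm. A reader of the results would see any suicide-related SAEs. They would not learn whether frequent suicidal thoughts became more or less common on one diet than on the other.

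The PHQ-9 total does not fill this gap. On a nine-item scale running from 0 to 27, each item carries at most 27 / 9 = 3 points. A participant who moves from the second to the fourth of the four responses on item 9 adds 2 points, which a modest improvement on the other eight items can offset. A fall in the total is therefore compatible with a rise in item 9. The documents do not show that this is likely; the plan simply could not reveal it.

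The stated reason for collecting only SAEs (protocol Section I.2) is that the ordinary side effects of ketogenic diets are well known. That reason does not extend to suicidality in people with treatment-resistant depression.

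**Working it through.** The plan gives no figure for its safety analysis. Its only design calculation, 64 participants for the primary outcome, reproduces: a two-sample t-test with difference 5, SD 6, two-sided 5% and 90% power needs 31.25 per group, rounded up to 32, so 2 × 32 = 64. It has no bearing on this point. The rest is a reading of the text with illustrative precision.

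**1. What is visible by arm under the plan**

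- Suicide-related event that meets the SAE definition: shown, descriptively (SAP 9).
- Significant but not imminent danger passed to the GP (protocol Section I.3): not shown.
- Item 9 at or above the level that triggers a risk assessment: not shown.
- Item 9 below that level: not shown.

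**2. Ascertainment over time**

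- Up to week 6, all participants are prompted for SAEs at the weekly calls (protocol Section I.1).
- At week 12, the question is about hospitalisation in the previous 6 weeks. A suicide-related event in that period without admission may not be recorded as an SAE.
- Item 9 at week 12 is the one scheduled response on suicidal thoughts after week 6. It looks back two weeks, so it covers about weeks 10 to 12. A response at the trigger level would lead to a risk assessment, which might itself bring an SAE to light.

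**3. The two wordings of a suicide-related SAE**

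- Protocol Section E: "Anyone judged to have a serious risk of suicide where an emergency response is initiated will be counted as having a serious adverse event". The condition is that a response was initiated, and counting is mandatory.
- Protocol Section I.1: other events "may also be considered a serious adverse event when, based upon appropriate medical judgement". The next sentence then says that a threatened suicide prevented by an emergency response is included. The condition here is prevention.

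A case in which a response was started, but no threatened suicide was clearly prevented, counts under Section E and is open under Section I.1. With SAEs expected to be very rare, one such case can change what is reported.

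**4. What SAE counts alone can say**

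Inputs: 88 randomised (SAP 2.2) at 1:1. The split is not given, so 88 / 2 = 44 per arm is assumed.

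- Upper one-sided 95% bound with no events: 1 − 0.05^(1/44) = 0.066, or 6.6%.
- Fisher's exact test, two-sided, 44 per arm: 0 v 5 gives p = 0.055; 0 v 6 gives p = 0.026. This only illustrates scale, since SAP 9 plans no test.

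**5. What an item-9 table could say**

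The 95% half-width for a difference in proportions at one visit is 1.96 × √(2p(1 − p)/44). No prevalence is given, so a range is assumed:

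- p = 10%: ±0.125, about ±13 points
- p = 20%: ±0.167, about ±17 points
- p = 30%: ±0.191, about ±19 points
- p = 40%: ±0.205, about ±20 points

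These figures assume no missing responses.

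**The case against.** A reader might infer that suicidality is never compared by arm. The documents do not support that: SAP 9 lists SAEs by type and counts them by arm, and SAP 3.2 describes that analysis as one diet against the other. Only suicidality below the SAE threshold lacks a summary. Nor is it unmonitored. Item 9 triggers individual assessment, contact is made the next working day (protocol Section I.3), and the steering committee reviews accruing data (Section L.2). That protects participants, but it does not tell readers how the arms compared.

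A reader might also infer that restricting safety to people who commenced a diet contradicts the plan, or removes crises. Neither follows. Protocol Section I.1 defines an adverse event as occurring in someone to whom a substance was administered, which gives the restriction a basis. Sessions attended and weekly rated adherence (SAP 4.4) could serve as proxies for starting. Nothing shows how many will not start, or that those in crisis are less likely to. What stands is that the term is undefined and that an SAE in a randomised non-starter could be collected and then left out. This is a separate weakness, not the cause of the missing item-9 summary.

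On the SAE wording, Section I.1 says that a prevented threatened suicide would be included, and this removes most of the apparent discretion. The mismatch between initiated and prevented remains, and it is small.

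Finally, the extra table is imprecise and would miss modest harm. That is true. Pooling visits is no remedy, because repeated responses from one person are correlated. The table should therefore be descriptive, and imprecision is no reason to leave it out.

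**Conclusion.** The point holds in a limited form. The plan as written cannot say whether frequent suicidal thoughts differed between arms unless they led to an SAE, although the risk is named in the protocol, the item is scheduled at five visits and a trigger level already exists. SAE-level suicidality is reported, but only descriptively, and its scheduled ascertainment is weakest after week 6.

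The size is one of information lost. No SAE among 44 leaves rates up to 6.6% open; the item-9 table would add estimates with half-widths of about 13 to 20 points. Both rest on an assumed 44 per arm, and the second also on an assumed prevalence of 10% to 40% and complete responses.

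A reader might go further and conclude that the plan conceals harm or that its efficacy result is in doubt. The documents support neither, and the primary analysis does not depend on any of this. It is an inexpensive improvement that the sponsor should make.

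**What to change.** - **SAP 9.** Add a descriptive table for all randomised participants in their allocated arm. At baseline and weeks 2, 4, 6 and 12 give the item-9 response distribution, the number at or above the protocol's existing trigger level, the number newly at or above it since baseline, and the number missing. Give confidence intervals and no hypothesis test.
- **SAP 9.** Add counts by arm of risk assessments, GP referrals and emergency responses where study logs hold them. Neither protocol Table 3 nor the SAP tables list a field for these, so availability should be checked first.
- **SAP 3.2.** Define commencement, and tabulate SAEs for all randomised participants by allocated arm beside that set, so that no collected SAE is left out.
- **Protocol Sections E and I.1.** Reconcile the two wordings of a suicide-related SAE. Which wording should stand is for the investigators to decide; this review proposes no clinical rule.

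The cost is SAP wording and one or two descriptive tables. Item 9 needs no new data collection. Because SAP section 10 indicates that primary-outcome output has already been reviewed, the additions should be dated and labelled as such. The drawback is that readers may over-read imprecise differences, which the confidence intervals should make plain.
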